**Results**

**Effective results:**

This study selected a total of 401 cases of patients with mild to moderate primary hypertension. After cleaning for 2 weeks, 283 subjects were randomly enrolled into groups, of whom there were 34 cases of dropping (12%) 7 cases were excluded (2.5%). The full analysis set included 279 cases (Allisartan Isoproxil with doses of 80, 160, 240mg and losartan of 50mg included 69, 68, 72, and 70 cases). The PPS included 246 cases (Allisartan Isoproxil with doses of 80, 160, 240mg and losartan of 50mg included were 60, 58, 67, 61 cases).

In FAS analysis, the sitting blood pressure (systolic/diastolic blood pressure) of the subjects treated with Allisartan Isoproxil of 80, 160, 240mg and losartan of 50mg for 4 weeks was 11.33/6.96, 11.35/6.35, 10.85/8.39, mmHg and 11.41/7.67mmHg less than that of the relative baseline. The sitting blood pressure (systolic/diastolic blood pressure) in various groups treated for 8 weeks was 9.12/6.30, 11.04/7.22, 11.76/8.57mmHg and 12.39/8.41mmHg was less than that of the relative baseline. The absolute decreasing value of the blood pressure increased with the increasing dose of Allisartan Isoproxil . The absolute decreasing value of the Allisartan Isoproxil (240 mg) was similar to that of the Losartan (50 mg), but there were no significant difference between groups.

After the treatment with Allisartan Isoproxil 80, 160, 240 mg and losartan of 50mg for 4 weeks, the percentrate of the standard meeting of the sitting blood pressure were 57.97%, 42.65%, 59.72% and 52.86%. The average decreasing values of the sitting blood pressure were decreased by 14.15/9.40, 15.17/11.41, 14.07/11.74mmHg and 18.57/12.84mmHg comparing with that of the baseline, but there was no significant difference between groups. After 8 weeks of treatment, compliance percentages of the sitting blood pressure were 43.48%, 52.94%, 58.33% and 54.29%, which were dropped by an average of 18.63/12.33, 20.06/13.22, 17.69/13.02 mmHg and 19.39/14.11mmHg comparing with that of the baseline, but there were no significant differences between groups.

90.32% of the subjects were mild hypertension. After treatment for 8 weeks with Allisartan Isoproxil with concentrations of 80, 160, 240mg and losartan of 50mg, the average sitting blood pressures were decreased by 8.18/5.84, 11.14/7.71, 12.48/8.82 and 12.22/7.89 mmHg comparing with that of the baseline.

After 8 weeks of treatment, the normal recovery percentages of the sitting blood pressure (SBP/DBP < 140mmHg/90mmHg) in the groups of Allisartan Isoproxil with concentrations of 80, 160, 240mg and losartan of 50mg were 39.13%, 47.06%, 50% and 44.29%. The average decreasing value of the sitting blood pressures were 18.07/12.11, 20.78/13.25, 18.03 /11.75mmHg and 20.42/13.65mmHg comparing with that of the baseline, but there were no significant differences among groups.

PP analysis was consistent with that of the FAS analysis results.

**Safety results:**

This study used a total of 282 cases of subjects with at least one drug treatment, who were all included in the safety analysis set, of whom the groups of Allisartan Isoproxil with 80 160, 240mg and losartan of 50mg were 70, 69, 73, 70 cases, respectively.

**（1）Adverse events**

The incidence rates of adverse events in the groups of Allisartan Isoproxil with 80 160, 240mg and losartan of 50mg were 32.86% (23/70), 27.54% (19/69), 30.149% (22/73) and 35.71% (25/70), mainly manifested as dizziness, headache, nausea, dizziness, abnormal blood lipid (including cholol, low density lipoprotein, glycerol three ), dysfunction of liver, urine protein and urine leucocyte abnormalities, of which the incidence rate of dizziness was the highest. In addition, the Allisartan Isoproxil (240mg) group had no abnormal blood lipids. All adverse events mainly demonstrated mild, some were moderate, which could be alleviated themselves or alleviated after symptomatic treatments. There was no significant difference in the incidence rate of adverse events and severe degrees among groups.

**（2）Adverse reactions**

The incidence rates of the adverse reactions in the groups of Allisartan Isoproxil with 80 160, 240mg and losartan of 50mg were 8.57% (6/70), 4.35% (3/69), 9.59% (7/73) and 10% (7/70), mainly manifested as headache, dizziness, headache, nausea, abnormal liver function, of which the incidence rates of headache (4.11%) and headache (2.74%) in the group of the Allisartan Isoproxil (240mg) were the highest. The incidence rates of dizziness, abnormal liver function abd nausea in each dose group were similar. The adverse reactions mainly exhibited as mild, some were moderate, which could be alleviated themselves or alleviated after symptomatic treatments. There was no significant difference in the incidence rate of adverse reactions and severe degrees among groups.

**（3）Important adverse events**

The incidence rates of the important adverse events in the groups of Allisartan Isoproxil (80, 160, 240mg) and losartan group (50mg) were 11.43% (8/70), 14.49% (10/69), 10.96% (8/73) and 15.71% (11/70), mainly manifested as headache, dizziness, headache, nausea, abnormal liver function. There was no significant difference in the incidence rate of he important adverse events among groups.

**（5）Laboratory tests, vital signs and physical examination**

After 8 weeks of treatment, the Allisartan Isoproxil group (160mg) had decreased neutrophil percentage, and increased percentrage of lymphocyte (statistically significant), but there was no significant difference among the groups in comparisons. There were significant differences in the platelet count between groups before and after treatments. After 8 weeks of treatment, the platelet count in the group of Losartan (50mg) increased and there was a significant difference. There was no statistical difference in the group of various doses of Allisartan Isoproxil before and after treatments.

After 8 weeks of treatment, triglyceride in the groups of Allisartan Isoproxil with 160 mg and 240 mg and the losartan group with 50 mg all decreased. The total cholol in the Allisartan Isoproxil group (80mg) was elevated. The high density lipoprotein in the Allisartan Isoproxil (240mg) group and the losartan group (50mg) were both increased, and there were significant differences. There was no significant difference of the above indexes before and after treatment between groups. In addition, there was no case of normal blood glucose, lipid and total cholol before treatment and abnormal after treatment on the above parameters only in the Allisartan Isoproxil group (240mg), but other experimental groups al had the case.

There was no significant difference in various indexes of liver functions before and after treatment and between groups, and there was no case with dysfunction of liver after treatment in the group of Allisartan Isoproxil (240 mg). After treatment with Allisartan Isoproxil (240 mg) for 4 weeks and 8 weeks, the level of creatinine was decreased (statistically significant); After treatment for 4 weeks, levels of uric acid in the groups of various doses of Allisartan Isoproxil and the group of Losartan (50 mg) were all reduced (statistically significant). After treatment for 8 weeks, levels of uric acid in the groups of Allisartan Isoproxil (80 mg, 240 mg) and the group of Losartan (50 mg) were all decreased (statistically significant); but there was no significant difference between the groups. After treatment for 4 weeks, levels of serum sodium and chlorine both increased in the group Losartan (50 mg), which was significantly different from that of the groups with different doses of Allisartan Isoproxil when comparing, but there was no significant difference between these groups in 8 weeks; the concentration of potassium was elevated after treatment with Allisartan Isoproxil (80 mg, 240 mg) for 4 weeks (statistically significant). The level of serum potassium was increased after treatment only with Allisartan Isoproxil (80 mg) for 8 weeks, but there was no significant difference between groups.

Of all the subjects with normal electrocardiogram before treatment, there were 2 patients had abnormal electrocardiogram treated for 8 weeks, and the related adverse events were recorded, which was diagnosed by 1 researcher that it was not related to the research drug, while another research believed that it was related to the research drug. There was no significant difference in the resting heart rate between different groups after treatments for 2, 4, 8 weeks.

# Research objective

## Primary objective

The primary objective was to compare the change of seated diastolic blood pressure from baseline to 8weeks in primary hypertensive patients with medium and low risks treated with 240 mg Allisartan Isoproxi tablet (ALS-3) and placebo to confirm the absolute antihypertensive effect of the Allisartan Isoproxi tablet (240 mg). Therapeutic effect index is the changes from baseline in trough mean seated DBP (23 to 26 hours after the morning dose) to the end of the 8-week double-blind treatment period

## Secondary objective

The secondary objective was to compare the following aspects of primary hypertensive patients at low-medium risk treated with 240 mg Allisartan Isoproxi tablet (ALS-3) and placebo:

- The change of trough mean seated DBP after 4 weeks treatment;
- The change of trough mean seated SBP after 4 ,8weeks treatment;
- Effective rate after 4,8 weeks treatment (Seated position SBP/DBP＜140mmHg/85mmHg, or SBP decreasing of 20 mm Hg and/or DBP decreasing 10 mm Hg);
- The change of trough mean seated SBP/DBP after 4 ,8weeks treatment in effective patient;
- Safety evaluation after 8 weeks.

# The expected duration of research, the number of research center and of the case number of planning

The present research program is planned to enroll subjects from May of 2009, and finish grouping in August of 2009, and statistical analysis and summary will be conducted in December of 2009.

Research will be carried out in 8 National Research center. The study designs 1 treatment group and 1 placebo group. One hundred and eight cases of patients in each group can be evaluated, so a total of 216 cases of patients are needed to be evaluated. Considering a shedding rate of 20%, a total of 260 qualified cases of subjects with hypertension are needed to be enrolled.

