**Protocol summary**

| **Protocol number** | TG0912ALS-3 |
| --- | --- |
| **Protocol name** | A Randomized, Double-Blind, Placebo-Controlled, Multicenter Phase II Clinical Trial of Allisartan Isoproxil in the Clinical Efficacy and Safety Treatment of Primary Hypertention Patients at Low-Medium Risk |
| **The version number/date** | The 1.2 eidtion, Aug, 06th, 2009 |
| **Sponsor** | Shenzhen Salubris Pharmaceuticals Co.,Ltd  Shanghai ALLIST Medicine Technology Co., Ltd. |
| **Clinical trial staging** | Phase II |
| **Indications** | Medium and lower risks of primary hypertension |
| **Experimental objective** | **The primary objective:**  The primary objective was to compare the change of seated diastolic blood pressure from baseline to 8weeks in primary hypertensive patients with medium and low risks treated with 240 mg Allisartan Isoproxi tablet (ALS-3) and placebo to confirm the absolute antihypertensive effect of the Allisartan Isoproxi tablet (240 mg).  **The secondary objective:**  The secondary objective was to compare the following aspects of primary hypertensive patients at low-medium risk treated with 240 mg Allisartan Isoproxi tablet (ALS-3) and placebo:   - The change of trough mean seated DBP after 4 weeks treatment; - The change of trough mean seated SBP after 4 ,8weeks treatment; - Effective rate after 4,8 weeks treatment (Seated position SBP/DBP＜140mmHg/85mmHg, or SBP decreasing of 20 mm Hg and/or DBP decreasing 10 mm Hg); - The change of trough mean seated SBP/DBP after 4 ,8weeks treatment in effective patient; - Safety evaluation after 8 weeks. |
| Experimental design | A randomized, double-blinded, placebo-controlled, multi center clinical trial |
| **Total number of cases** | There was 1 treatment group and 1 placebo group. One hundred and eight cases of patients in each group can be evaluated, and a total of 216 cases of patients can be evaluated. Considering a loss rate of 20%, a total of 260 subjects were needed to be enrolled. |
| **Research center number** | Eight |

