| **Statistical analysis** | **Estimation of sample sizes:**  This is a superior efficacy test study. The efficiency test was conducted on the main therapeutic effect index. Setting bilateral α = 0.05, *β* = 0.20, and the standard deviation SD = 7.8 mmHg, the difference of the antihypertensive effect in the two groups were detected as *D* = 3 mmHg. The distribution ratio of the patient cases in the two groups was 1:1. The estimated minimum sample size was 108 pairs. Taking into account of the factors such as dropping, the present research plan included 260 cases into the two groups with 130 cases of patients in the experiment group and the control group, respectively.  **Statistical analysis of the data set:**  Statistical analysis was conducted by using the full analysis set, per-protocol population set and safety data set. The quality control was strictly carried out in the whole process of the data statistics to ensure the authenticity of the assessment of data.  Full analysis set (Full analysis set, FAS): according to the fundamental principle of intention to treat (ITT), all the randomly enrolled subjects with more than one medication administration record and effective evaluation were included in the full analysis set. When selecting full analysis set for analysis, the latest observation LOCF (LOCF) estimation method was adopted for the estimation of the missing values. Full analysis set is the main effectiveness method for the evaluation of population in the present study.  The Per-Protocol set (PPS): PPS included all the subjects with completed prescribed treatment protocal or no serious violations of tests. The exact definition of the serious violations of the scheme will ultimately determined in the data auditing, which generally included the following situations (but they are not limited to these cases): Not meeting the inclusion criteria, having interference treatment after being selected, poor compliance, interview beyond the time window. PP set is a secondary analysis of the crowds of the effectiveness, but if the results were inconsistent with the full analysis set, detailed analysis should be done on the inconsistent results.  Safety data set (Safety Set, SS): the definition of safety data set was the subjects that at least received one time drug treatment.  **Statistical analysis method:**  Statistical analysis was conducted by using the SAS9.13 statistical analysis software for calculation. Quantitative description of the parameters included the calculation of mean, standard deviation, median, minimum value and maximum value. The description of the classified index employed the case number and percentage of the cases.  Descriptive statistics were conducted on the completion of the study. The comparison among groups was conducted on the demographic and baseline characteristics to analyze the equilibrium between groups.  Analysis of the main outcome measures: the main efficacy index will use the test of superiority. In addition, the dereasee value os DBP of each subject after treatment of 8 weeks will also be calculated, and descriptions in each group were done (mean, standard deviation, median, minimum, maximum). Comparisons between groups used analysis of variance considering center effect.  Analysis of the secondary outcome indicators: the center effect was not considered in principle. Comparisons between groups employed the variance analysis, chi-square test or nonparametric statistical method.  Analysis of the safety evaluation: parameters of safety evaluation included adverse events/ adverse drug reaction (ADR)/important adverse events or serious adverse events, physical examination and laboratory examination and a 12-lead electrocardiogram. Detailed description was conducted on the cases of adverse events during the test. The incidence rates of the adverse events between the two groups were summarized and compared. The indexes of laboratory examination were statistically described. The difference between two groups was compared when it was necessary. A detailed description of the laboratory indexes and normal cases before treatments was conducted.  This study did not conduct interim analysis. |

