# Statistics

## Sample size estimation

This study is the research on high efficiency, the efficiency test of the main therapeutic effect index. A: bilateral α = 0.05, P = 0.20, the standard deviation of the difference between SD=7.8mmHg and D detected two groups of antihypertensive effect of = 3mmHg, two cases of the distribution ratio of 1:1, the estimated minimum sample size was 108, taking into account factors such as the research plan off, 260 cases into two groups, the experiment group and the control group with 130 cases in each. The estimation results of PASS2008 software sample:

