**Numeric Results for Superiority Test (H0: D <= |E|; H1: D > |E|)**

**Test Statistic: T-Test**

|  |  | **Equivalence** | **Actual** | **Significance** |  | **Standard** | **Standard** |
| --- | --- | --- | --- | --- | --- | --- | --- |
|  |  | **Margin** | **Difference** | **Level** |  | **Deviation1** | **Deviation2** |
| **Power** | **N1/N2** | **(E)** | **(D)** | **(Alpha)** | **Beta** | **(SD1)** | **(SD2)** |
| 0.80229 | 108/108 | 0.00 | 3.00 | 0.02500 | 0.19771 | 7.80 | 7.80 |

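### 260 enrolled covers a loss of at most 16.9%, not the stated 20%; a 20% loss leaves 208 evaluable patients, not 216

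*Protocol*

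**What the plan says.** Section 3 of the protocol plans 108 evaluable patients per group, 216 in all, and continues: "Considering a shedding rate of 20%, a total of 260 qualified cases of subjects with hypertension are needed to be enrolled". The synopsis row on the total number of cases gives the same sum: "Considering a loss rate of 20%, a total of 260 subjects were needed to be enrolled".

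Section 11.1 supplies the base number. Its inputs are "bilateral α = 0.05, P = 0.20" (the second figure stands for β, as the synopsis shows), a 3 mmHg difference, and, in the synopsis wording, "the standard deviation SD = 7.8 mmHg". The PASS output for a two-sample t-test reads "0.80229 | 108/108 | 0.00 | 3.00 | 0.02500 | 0.19771 | 7.80 | 7.80". Section 11.1 and the synopsis paragraph on sample size call 108 the minimum and then go to 260 (130 per group) to allow for dropouts, without giving a percentage.

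Section 11.2 makes the full analysis set (FAS) the main efficacy population. It consists of randomised patients with medication records and an efficacy evaluation, and allows missing values to be filled by last observation carried forward (LOCF).

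**The concern.** Four numbers are fixed together: 216 evaluable, 20% lost, 260 enrolled and 80% power. They do not fit one another. Removing 20% of 260 does not leave 216, and the protocol itself describes 108 per group as the smallest adequate size, so no reserve absorbs the gap. A reader of the synopsis or section 3 would believe that the trial tolerates one patient in five being lost before power drops below 80%. In fact it tolerates about one in six.

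**Working it through.** **Inputs.** Difference D = 3 mmHg, SD = 7.8 mmHg in each group, two-sided α = 0.05 (run as one-sided 0.025), allocation 1:1, two-sample t-test (section 11.1 and its PASS output). Required evaluable: 108 per group, 216 in total. Loss 20%, enrolment 260 (section 3 and synopsis).

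**Step 1: reproduce the base number.** With n per group, the noncentrality is D / (SD × √(2/n)) on 2n − 2 degrees of freedom, and power is the probability that a noncentral t exceeds the 0.975 quantile of the central t.

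- n = 107: power 0.7997
- n = 108: noncentrality 3 / (7.8 × √(2/108)) = 2.83, power 0.803 (PASS prints 0.80229)

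So 108 is the smallest n that reaches 80%. The base number and its power reproduce.

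**Step 2: reproduce the enrolment figure.**

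- Multiplying: 216 × (1 + 0.20) = 259.2, rounded up to 260. This matches the protocol.
- Dividing: 216 / (1 − 0.20) = 270 (135 per group). This does not match; it is 10 patients more.

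The protocol's 260 is obtained only by multiplying.

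**Step 3: what 260 delivers.**

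- Evaluable at 20% loss: 260 × 0.80 = 208, or 104 per group, which is 8 short of 216.
- Largest loss that still leaves 216: (260 − 216) / 260 = 44/260 = 16.9%.

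**Step 4: power at 104 per group.** Noncentrality 3 / (7.8 × √(2/104)) = 2.77, power 0.788. The same calculation gives 0.803 at 108, a difference of 1.5 points. By the normal approximation the pair is 0.792 and 0.807, so the size of the drop does not depend on the method.

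**Step 5: which denominator the protocol uses for loss.** The results of the earlier phase II trial in section 1.2 report 283 randomised, 34 dropouts (12%) and 7 exclusions (2.5%). 34/283 = 12.0% and 7/283 = 2.5%, so the protocol expresses loss as a share of those randomised. On that definition division by 0.80 is the right step.

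**The case against.** The strongest reply is that the 20% does not act on the primary analysis. A patient who leaves early but has an efficacy evaluation stays in the FAS, with LOCF filling the week 8 value. The only retention data in the protocol point the same way. In the earlier trial the FAS held 279 of 283 and the per-protocol set 246 of 283. Applied to 260, those fractions give 260 × 279/283 ≈ 256 (128 per group, power 86.5%) and 260 × 246/283 ≈ 226 (113 per group, power 82.1%), both above 216.

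This stands as a limit on the consequence. A reader might infer that the primary comparison will end with 208 patients and less than 80% power. The documents do not support that, because nothing in section 11.2 says that every dropout leaves the FAS. Two cautions apply to the reassurance. The earlier trial was active-controlled, and placebo patients may leave at a different rate. The power figures also assume that carried-forward values have the same 3 mmHg difference and 7.8 mmHg SD. In any case, the reply does not repair the sentence: if far fewer than 20% are expected to be lost from the analysis, then 20% is the number that needs correcting.

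A second reply is that 20% could mean one fifth added on top of 216. The protocol's own reporting of loss as a share of those randomised argues against this, and both sentences call it a rate of loss or shedding.

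A third reply is that the effect is small and the statistical section attaches no percentage to 260. Both are true. The error is confined to one statement, which appears in the synopsis and in section 3.

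**Conclusion.** A minor arithmetic error, certain as written. The 260 was obtained by multiplying by 1.2 instead of dividing by 0.80. It secures 216 evaluable patients only up to a 16.9% loss. At the stated 20% loss of evaluable patients, 208 remain and power is 78.8%, not 80%. That power assumes equal loss in both groups (104 each), D = 3 mmHg, SD = 7.8 mmHg and a t-test at two-sided 0.05.

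The shortfall belongs to evaluable patients as the synopsis and section 3 count them. It is not evidence that the primary FAS analysis is underpowered, nor that more patients must be enrolled. It might also be taken as a fault in the PASS output, but that output refers to 108 per group and is correct.

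**What to change.** Keep 260 and correct the sentence in the synopsis row on the total number of cases and in section 3, for example:

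> Enrolling 260 patients yields 216 evaluable patients at a loss of up to 16.9%; at a loss of 20%, 208 would be evaluable and power would be 78.8%.

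A clause noting that the FAS with LOCF retains dropouts who have an efficacy evaluation would help the reader. The earlier trial's dropouts and exclusions should not be added up and offered as an expected evaluable loss: 283 − 34 − 7 = 242 matches neither its FAS (279) nor its per-protocol set (246). Section 11.1 and the PASS output stay as they are.

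The cost is wording only, with no added patients and no change to the analysis; the stated loss allowance becomes slightly less favourable. If the sponsor prefers to keep the 20% allowance, the consistent enrolment is 270 (135 per group), 10 more than planned.
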